### Sample size and eligibility criteria

2.2

One-hundred and twenty subjects (WP1: 100 subjects; WP2: 20 subjects) who are diagnosed with major depressive episode (both during the course of MDD or bipolar disorder) according to the Diagnostic and Statistical Manual of Mental Disorders, 5th edition (24), will be recruited by three Research Units: the ‘G. d’Annunzio’ University of Chieti, the University of Milano, and the Tor Vergata University of Rome.

The inclusion criteria will be the following: age between 18 and 65; current major depressive episode within at least the past month; TRD, defined as the absence of clinical response despite two or more treatments with antidepressants at adequate doses for 4-6 weeks (5); current stable psychopharmacological therapy for at least 1 month.

The exclusion criteria will be the following: presence of severe organic or neurological comorbidities, any substance use disorder (except nicotine dependence) in the past 6 months, intellectual disability or decline (Mini-Mental State Examination, MMSE < 26); uncontrolled systemic hypertension (specific for safety of ESK-NS treatment); presence of a positive history of seizures in the patient’s history or a first-degree relative (specific for arTMS safety); pregnant and postpartum women.

To refine the processing precision of the tool, we will consolidate the dataset from participants enrolled in the study with clinical data gathered retrospectively. These supplemental data will be obtained from a dedicated TRD dataset, which includes information from subjects who met identical inclusion and exclusion criteria and underwent prior treatment in our centers with ESK-NS (n = 50) and arTMS (n = 50).

### Study schedule

2.3

The enrolled patients will undergo a comprehensive clinical examination as the initial step. Electrophysiological (EEG recordings) and peripheral biomarkers will be collected during this process. The administration of ESK-NS or arTMS will be determined according to the groupings of participants. Specifically, in the first phase, subjects will be randomly assigned to arTMS or ESK-NS. In the second phase, the extracted treatment-orienting biomarkers will be introduced in the SelecTool model as input data. Based on the SelecTool output, subjects will be assigned to the ESK-NS or arTMS interventions.

Baseline and 1-month follow-up assessments will include neuropsychological and psychiatric evaluations, behavioral assessments, neurophysiological data acquisition, and the collection of peripheral biomarkers.

After one month, the clinical response will be measured by a blind rater based on the MADRS score (> 50% reduction).

### Neuropsychological and psychiatric assessment

2.4

Subjects will undergo assessments at the screening visit (T0) and one month after initiation of treatment (T1) using a battery of validated psychometric tests (**Table 1**). At baseline, collection of anamnestic data will include sociodemographic factors, the history of depressive illness, treatment history for the current major depressive episode (MDE), comorbidities, lifetime antidepressant trials, augmentation strategies (such as the combined use of mood stabilizers, benzodiazepines, or antipsychotics), and other therapeutic interventions for treating treatment-resistant depression (TRD). These evaluations will be conducted by qualified psychiatrists, residents in psychiatry or clinical psychologists blinded to the treatment assignment. The primary outcome will be assessed in terms of clinical response, measured by the Montgomery-Åsberg Depression Rating Scale (MADRS; score reduction > 50%) (25). Patients will be evaluated for mood (Hamilton Depression Scale; Young Mania Rating Scale) (26), anhedonia (Snaith-Hamilton Pleasure Scale) (27), temperamental aspects (Temperament Evaluation of Memphis, Pisa and San Diego Autoquestionnaire version) (28); Barratt Impulsiveness Scale version 11; Big Five Questionnaire) (29, 30), anxiety (Hamilton Anxiety Scale) (31), alexithymia (Toronto Alexithymia Scale) (32), general psychiatric symptoms (Brief Psychiatric Rating Scale) (33), traumatic experiences (Childhood Trauma Questionnaire) (34), suicide risk (Columbia-Suicide Severity Rating Scale, Beck Hopelessness Scale) (35, 36), and resilience (Connor-Davidson Resilience Scale) (37). Health-related assessments will use the Clinical Global Impression-Severity scale (CGI-S) (38).

**Table 1 T1:** Psychometric assessment at T0 and T1.

Psychometric assessment	
Mood	*Hamilton Depression Scale* *Young Mania Rating Scale*
Anhedonia	*Snaith-Hamilton Pleasure Scale*
Temperamental aspects	*Temperament Evaluation of Memphis, Pisa and San Diego Autoquestionnaire version* *Big Five Questionnaire*
Anxiety	*Hamilton Anxiety Scale*
Alexithymia	*Toronto Alexithymia Scale*
General psychiatric symptomatology	*Brief Psychiatric Rating Scale*
Traumatic experiences	*Childhood Trauma Questionnaire*
Suicide risk	*Columbia-Suicide Severity Rating Scale*
Resilience	*Connor-Davidson Resilience Scale*
Health-related assessments	*Clinical Global Impression-Severity scale Health Status Questionnaire*

### Behavioral evaluation

2.5

A comprehensive neuropsychological evaluation targeting various cognitive functions will be conducted for all patients. The assessment battery will primarily encompass measures of global cognition (MMSE) (39), attention (sustained spatial attention, Trail Making Test-A [TMT-A]; divided spatial attention, TMT-B; cognitive flexibility, TMT-AB) (40), short- and long-term episodic memory (Babcock Memory test) (41), and executive function (Frontal Assessment Battery) (42).

### Neurophysiological data

2.6

At T0 and T1, EEG electrical activity will be acquired utilizing a 64-channel EEG system (eego™mylab; ANT Neuro, Hengelo, Netherlands). Resting-state EEG will be recorded with eyes open and closed. Electrooculography and electrocardiography will also be acquired using additional electrodes. The data will undergo pre-processing to eliminate sections of poor quality and channels with unreliable data. Independent component analysis will be applied to eliminate periodic, non-brain signals. EEG analysis aims to identify pertinent and effective electro-neurophysiological biomarkers (at the channel/scalp, source, and source connectivity levels) indicative of treatment response in TRD (**Table 2**).

**Table 2 T2:** EEG biomarkers to predict treatment response.

**Alpha asymmetry**	Based on the approach-withdraw model (43), this measures relative alpha band activity between brain hemispheres (mainly in frontal regions; higher alpha may reflect lower brain activity). Alpha asymmetry has been proposed as a suitable prognostic biomarker related to anxious subtype and bipolar features (44).
**Microstate abnormalities**	Using polarity-insensitive k-mean clustering, we will segment resting-state high-density EEG data into microstates (45). The proportion, duration, occurrence, and transition of microstates will be studied as potential biomarkers of state and trait abnormalities and as predictors of treatment outcome.
**Rostral anterior cingulate cortex theta activity**	This is a robust marker that predicts greater improvement in selective serotonin reuptake inhibitor-induced depressive symptom (46).
**Subgenual/prefrontal connectivity**	Based on recent findings that suggest that changes in rTMS-induced within-network connectivity are a mediator of treatment response (47), eLORETA linear-lagged connectivity measures of theta (4-7.5 Hz) and alpha (8-13 Hz) frequency will be obtained between the following regions of interest: right and left DLPFC, dorsomedial prefrontal cortex, and subgenual cingulate cortex (as in Iseger et al, 2017).
**Gamma-band power envelope connectivity**	Orthogonalized power envelope correlation will measure EEG source connectivity (48). Large-scale connectivity patterns have been proposed as predictors of placebo/antidepressant outcomes.

### Peripheral biomarkers

2.7

Blood samples (15 ml) will be collected at T0 and T1 by forearm venipuncture after an overnight fast. These samples will be stored in BD Vacutainer tubes containing ethylenediaminetetraacetic acid. Serum and plasma will be prepared by centrifugation at 1500 rpm for 10 minutes at 4°C. The serum will be stored in 0.5 ml Eppendorf tubes at -80°C until analysis.

Enzyme-linked immunosorbent assays (ELISAs) will be used to assess systemic inflammation and oxidative stress markers, including C-reactive protein, interleukin-1b (IL-1b), IL-5, IL-6, IL-8, and tumor necrosis factor-alpha (TNF-alpha). The levels of cortisol and adrenocorticotropic hormone will be determined using ELISA. Using specific monoclonal antibodies, the levels of TSH, FT3, and FT4 will be determined. Plasma brain-derived neurotrophic factor (BDNF) and proBDNF levels as biomarkers of synaptic integrity and plasticity will be investigated using ultra-sensitive high-performance single-molecule arrays or conventional ELISA.

### Treatment administration

2.8

During the first phase (WP1), subjects will be randomly assigned in a 1:1 ratio to receive arTMS or ESK-NS. A stratified randomization approach with a four-block size will be implemented to minimize inadvertent bias. Stratification factors will include sex (male, female), age (expected cutoff 50 years old), depression severity (mild/moderate depression, MADRS ≤ 34; severe depression, > 34), and treatment site (Chieti, Milan, and Rome). The randomization process will be carried out by an investigator external to the study.

In the pilot validation phase (WP2), the extracted treatment-guiding biomarkers will be incorporated into the SelecTool model as input data. Subsequently, subjects will be allocated to esketamine or arTMS interventions based on the output of the SelecTool.

All subjects will undergo a comprehensive preliminary visit to assess potential contraindications to treatments. Qualified medical personnel, specifically trained to handle potential side effects and emergencies related to treatments, will administer ESK-NS and arTMS treatments.

Subjects in the ESK-NS group will be administered the drug according to the EMA guidelines (49). It will be supplied in a double-use nasal spray device containing 200 μl of vehicle solution (two sprays), each delivering 28 mg (14 mg ESK-NS base per 100 μl of spray). This dose will be administered twice a week for the first week, followed by 84 mg (three devices) administered twice a week for three weeks, resulting in a total of 1 month of treatment. Before initial administration, patients will be instructed to blow their nose (only before the first device is administered) and then assisted to recline their head 45° (semi-reclined position) during administration to enhance retention of the medication within the nasal cavity. Each ESK-NS session will be conducted by qualified personnel who closely monitor vital parameters (blood pressure, heart rate) before and at 45 and 90 minutes after treatment, following international safety guidelines (50).

Patients in the arTMS group will undergo a 5-day arTMS protocol involving four daily sessions (8). This protocol, developed following the safety guidelines (51) and the principles of accelerated protocols (52), aims to deliver the same number of magnetic pulses as the FDA-approved protocol (53). Stimulation will be performed using a MagPro R30 (MagVenture) system with a B-70 coil targeting the left dorsolateral prefrontal cortex (L-DLPFC), a region approved for TRD treatment (53). The L-DLPFC will be identified using the BEAM F3 method (54), facilitating rapid localization through anthropometric measures. The resting motor threshold will be determined using the evoked potential motor method (55). Each session will adhere to the following parameters, aligning with the FDA-approved standard (53): 10 Hz frequency, 120% resting motor threshold, 40 pulses/train (4 s duration), 26 s inter-train interval, 3000 pulses/session, and a total duration of 35 minutes. This session will be repeated four times within the same day, with a 55-minute interval between sessions (total duration of the cycle session pause: 90 minutes), thus adhering to the accelerated stimulation protocol. The entire protocol will take approximately 5 hours and 5 minutes. Throughout this time, patients will be continuously monitored for side effects. The onset of potential side effects will be evaluated at each stimulation session using a specific and approved scale for rTMS-related side effects (56).

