## Abstract

Treatment-Resistant Depression (TRD) poses a substantial health and economic challenge, persisting as a major concern despite decades of extensive research into novel treatment modalities. The considerable heterogeneity in TRD’s clinical manifestations and neurobiological bases has complicated efforts toward effective interventions. Recognizing the need for precise biomarkers to guide treatment choices in TRD, herein we introduce the SelecTool Project. This initiative focuses on developing (WorkPlane 1/WP1) and conducting preliminary validation (WorkPlane 2/WP2) of a computational tool (SelecTool) that integrates clinical data, neurophysiological (EEG) and peripheral (blood sample) biomarkers through a machine-learning framework designed to optimize TRD treatment protocols. The SelecTool project aims to enhance clinical decision-making by enabling the selection of personalized interventions. It leverages multi-modal data analysis to navigate treatment choices towards two validated therapeutic options for TRD: esketamine nasal spray (ESK-NS) and accelerated repetitive Transcranial Magnetic Stimulation (arTMS). In WP1, 100 subjects with TRD will be randomized to receive either ESK-NS or arTMS, with comprehensive evaluations encompassing neurophysiological (EEG), clinical (psychometric scales), and peripheral (blood samples) assessments both at baseline (T0) and one month post-treatment initiation (T1). WP2 will utilize the data collected in WP1 to train the SelecTool algorithm, followed by its application in a second, out-of-sample cohort of 20 TRD subjects, assigning treatments based on the tool’s recommendations. Ultimately, this research seeks to revolutionize the treatment of TRD by employing advanced machine learning strategies and thorough data analysis, aimed at unraveling the complex neurobiological landscape of depression. This effort is expected to provide pivotal insights that will promote the development of more effective and individually tailored treatment strategies, thus addressing a significant void in current TRD management and potentially reducing its profound societal and economic burdens.

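### A single stated block size of four within 24 strata that include site could let site staff know up to about a quarter of WP1 allocations in advance

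*Protocol article*

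**What the plan says.** Section 2.8 (Treatment administration) of the protocol article describes allocation in WP1. Patients are allocated equally: "subjects will be randomly assigned in a 1:1 ratio to receive arTMS or ESK-NS". The scheme is given in one sentence: "A stratified randomization approach with a four-block size will be implemented to minimize inadvertent bias". Only one block size is named, and no variation is mentioned.

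The factors follow: "Stratification factors will include sex (male, female), age (expected cutoff 50 years old), depression severity", the last split at a MADRS score of 34, and then treatment site with three levels. On who operates the scheme, the section says: "The randomization process will be carried out by an investigator external to the study".

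The Abstract gives the number randomised: "In WP1, 100 subjects with TRD will be randomized to receive either ESK-NS or arTMS". Blinding is described for the assessors only. Section 2.4 has the evaluations done by "qualified psychiatrists, residents in psychiatry or clinical psychologists blinded to the treatment assignment", and section 2.3 has a blind rater measure response. One arm receives a nasal spray over a month and the other receives coil stimulation over five days. No sham or double dummy is described.

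**The concern.** In a permuted block of four with two arms, once one arm's two places are used, the rest of the block is fixed. Anyone who knows the block size and sees earlier allocations in that stratum can work this out. Both conditions could be met here. The treatments cannot be mistaken for one another, and because site is a stratification factor, each site's sequences depend only on its own patients. A site needs to follow just its own eight cells.

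The protections described act elsewhere. An external randomiser hides the list but not the count. Blinded raters protect outcome measurement, not enrolment. Before treatment there is also a clinical screen that leaves some room for judgement: "All subjects will undergo a comprehensive preliminary visit to assess potential contraindications to treatments". Someone who foresees the next arm could enrol, defer or decline a patient accordingly.

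What is at stake is WP1's role. The other 100 training patients (section 2.2) are retrospective, with no randomisation described, so WP1 is the only randomised comparison of the two treatments. Section 2.1 also compares WP2 response with response under random assignment, so selection in WP1 would affect that benchmark.

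**Working it through.** The article gives no figure for predictability, so there is none to reproduce.

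**Inputs from the article.** Two arms, 1:1; block size 4; sex 2, age 2, severity 2 and site 3 levels (section 2.8); 100 randomised patients (Abstract).

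**Assumption.** The spread of patients over strata is not given. The base case is an equal split. The range runs to a heavy skew: sex 70/30, age 70/30, severity 80/20, sites 60/25/15.

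**Step 1, strata.** 2 × 2 × 2 × 3 = 24, or 8 per site. 100 / 24 = 4.17 patients per stratum.

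**Step 2, one completed block.** The six equally likely sequences are AABB, ABAB, ABBA, BAAB, BABA and BBAA. The next allocation is certain when only one arm has places left.
- Positions 1 and 2: never.
- Position 3: only in AABB and BBAA, 2/6 = 1/3.
- Position 4: always.

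Expected certain places = 0 + 0 + 1/3 + 1 = 4/3, and (4/3) / 4 = 33.3%.

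**Step 3, all of WP1.** A stratum with n = 4q + r patients has on average (4/3)q + c(r) certain allocations, where c(0) = c(1) = c(2) = 0 and c(3) = 1/3. Each stratum count is taken as Binomial(100, p), with p that stratum's share. The expectation is summed over the 24 strata and divided by 100.
- Equal strata: 23.2%, about 23 of 100 patients.
- Skewed splits: 23.2% to 24.8%.

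**Step 4, best guess.** Guessing the arm with more places left is right with probability 1/2, 2/3, 2/3 and 1 by position. The mean is 70.8% in a completed block. Over 24 equal strata it is 66.3%, against 50% by chance.

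**Step 5, alternatives.** These were simulated with equal strata and an observer who sees every earlier allocation in the stratum and knows the set of possible block sizes, but not the current size.

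| Strata | Block sizes | Known with certainty | Best guess correct |
|---|---|---|---|
| 24 | 4 (as planned) | 23.2% | 66.3% |
| 24 | 2, 4 | 7.8% | 68.3% |
| 24 | 4, 6 | 3.7% | 64.0% |
| 24 | 2, 4, 6 | 1.7% | 65.7% |
| 6 | 4 | 30.8% | 69.7% |
| 6 | 2, 4 | 10.5% | 71.2% |
| 6 | 4, 6 | 6.1% | 68.1% |
| 6 | 2, 4, 6 | 3.4% | 69.2% |

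Varying the block size removes most of the certainty. Cutting the strata to six does the opposite: each row is more predictable than its 24-stratum counterpart, because more blocks are completed.

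**Step 6, minimisation.** If the balancing arm is chosen with probability 80%, no allocation is certain. Simulated with the same four factors, best-guess accuracy is about 61% for someone who sees only their own site, and about three quarters for someone who sees all three.

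**The case against.** The strongest reply is that 23–25% is a ceiling. To reach it, a recruiter must know the block size, keep a tally for eight cells, know each earlier allocation and know the candidate's severity stratum before enrolment. The article does not say that recruiters deliver treatment, and its clinical assessors are blinded. It does not use the term open-label; visibility is inferred from the treatments. It gives no recruitment dates, so it is unknown whether sites knew the block size while enrolling. All of this stands, and the figure should be read as what could be known, not what will be.

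The opening for judgement is also limited. Section 2.2 applies the safety exclusions specific to each treatment to everyone, and the preliminary visit covers both treatments. No eligibility rule depends on the arm. Timing and borderline judgements remain.

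Four stronger readings are tempting, and the document does not support them.
- **That the tool learns the allocation pattern.** Section 2.9 trains the model to predict outcome, not treatment. Selection on measured features that enter the model need not bias prediction given those features; selection on unmeasured prognosis could. No size of bias can be derived.
- **That this is the main threat to the training data.** Half of the pooled 200 patients are retrospective, with no randomisation described. Predictable allocations in the other half are a smaller matter.
- **That unfinished blocks do serious harm.** About 18 of 24 strata would end with one (16.2 to 18.3 over the range), but no stratum is then off by more than 2. The overall arm difference has a standard deviation of about 4.4 patients, against √100 = 10 under simple randomisation.
- **That there are too many strata.** Fewer strata with the block still at four would raise certain allocations to 30.8%.

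**Conclusion.** The point holds as a modest, cheaply corrected weakness. With one fixed block of four in 24 strata that include site, staff who know the block size and tally could know up to about 23–25% of WP1 allocations with certainty, and 33% in completed blocks. This rests on the stated design, on treatments that staff can tell apart, and on the assumed stratum splits, over which the result is stable. External randomisation and blinded raters do not change it.

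A reader might infer that WP1 is biased or that the tool would be invalid. Nothing in the document shows that anyone will use the predictability, and no effect on outcome is quantified. The conclusion is only that an avoidable route to selection is left open in the project's one randomised comparison, which is also the benchmark for WP2.

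**What to change.** Keep the four stratification factors. Replace the fixed block of four with block sizes drawn at random, for example from 4 and 6 or from 2, 4 and 6, generated by the external investigator and not disclosed to the sites until recruitment ends. Certain allocations then fall from about 23% to between 2% and 8%, depending on the sizes chosen, even if a site knows the set. Minimisation on the same factors with a random element, such as an 80% probability for the balancing arm, is an acceptable alternative.

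The cost is a new randomisation specification and list, with no extra patients or visits. If recruitment has begun, the new list can serve the remaining patients and the change can be reported. Within-stratum balance may be slightly looser: an unfinished block of six can leave a stratum off by 3 instead of 2. Best-guess accuracy will not improve much. It stays at about 64–68% across the varying-block options with 24 strata, against 66% now, so the benefit to claim is the loss of certainty, not the end of guessing.

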### Statistical analysis

2.9

Drawing from the existing literature on the efficacy of arTMS and ESK-NS for Treatment-Resistant Depression (TRD), we anticipate a response rate of approximately 50% for each treatment (52, 57). The sample size was determined using the G*Power 3.1 software, taking into account specific parameters: a substantial effect size of predictors (expected Cohen effect size F = 0.4), power 1-beta = 0.80, one-way, four groups (2x2; treatment: ESK-NS, arTMS; responders and non-responders), and a significance level corrected for multiple comparisons (alpha = 0.001). These calculations resulted in a total sample size of n = 144. Considering a possible imbalance in the allocation of responders (10%) and to mitigate possible dropouts (10%), we increased the total sample size to n = 200.

We will develop a machine-learning model to predict the primary treatment outcome and use it for treatment guidance. This model will leverage both neurophysiological data and clinical scores. We also aim to interpret the model and extract the features that influence it. Given the heterogeneous nature of the collected data, an appropriate solution is to opt for ensemble methods, particularly random forest techniques, which have shown suitability for such tasks (19, p. 202) and are relevant for *post hoc* analysis of results. To provide comprehensive insights, our exploration will not be restricted to random forest techniques; we will also investigate other approaches such as neural networks or support vector classifiers. Dealing with missing values in clinical and psychometric tests is a critical concern, and we will address this using advanced techniques such as multivariate imputation (58, 59). The model parameters and performance will be assessed using nested and shuffle cross-validation, which is recognized as optimal to minimize bias in model error estimations (60). The results’ significance will be evaluated using permutation tests, which are acknowledged as the gold standard for statistical assessments of machine-learning algorithms (61).

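### The 80% power in section 2.9 belongs to a one-way four-group comparison that the article does not describe, and does not carry over to the permutation test of the classifier that it does describe

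*Protocol article*

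**What the plan says.** Section 2.9 (Statistical analysis) of the protocol article has two paragraphs that bear on this.

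The first is the sample-size calculation. Its inputs are "a substantial effect size of predictors (expected Cohen effect size F = 0.4), power 1-beta = 0.80, one-way, four groups", the groups being "four groups (2x2; treatment: ESK-NS, arTMS; responders and non-responders", with "a significance level corrected for multiple comparisons (alpha = 0.001". It continues: "These calculations resulted in a total sample size of n = 144". The inflation follows: "Considering a possible imbalance in the allocation of responders (10%) and to mitigate possible dropouts (10%), we increased the total sample size to n = 200".

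The second is the analysis: a model that predicts response, with random forest preferred and neural networks and support vector classifiers also to be tried. On evaluation it says "The model parameters and performance will be assessed using nested and shuffle cross-validation" and "The results’ significance will be evaluated using permutation tests". It gives no alpha, performance metric, number of inputs or target performance for the permutation test.

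**The concern.** The two paragraphs concern different tests. The calculation compares the mean of one predictor across four treatment-by-response groups; its null hypothesis is that the four means are equal. The described analysis combines many inputs in a classifier, scores it on held-out folds and compares that score with its permutation distribution; its null is that the inputs carry no information about response. The statistic and the null hypothesis differ, and the 0.001 is not tied to the permutation test.

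The 80% is the only power figure in the article, so readers will attach it to the SelecTool model. A non-significant permutation result could then be taken as evidence against the tool from a study with 80% power, when the true chance of significance may have been much lower. Nor can anyone tell from the text whether it was lower.

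**Working it through.** **1. The plan's own figure.** Inputs from section 2.9: f = 0.4, k = 4 groups, alpha = 0.001, power 0.80. For a fixed-effects one-way ANOVA, df1 = k - 1 = 3, df2 = N - 4, and the noncentrality is lambda = f² × N = 0.16N.

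| N | lambda | critical F (0.001) | power |
|---|---|---|---|
| 142 | 22.72 | 5.733 | 0.796 |
| 143 | 22.88 | 5.731 | 0.801 |
| 144 | 23.04 | 5.728 | 0.805 |
| 200 | 32.00 | 5.639 | 0.957 |

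The smallest N is 143, or 144 with equal groups. The printed 144 reproduces exactly, so the 80% is the power for one predictor in a four-group ANOVA.

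**2. What f = 0.4 means for a classifier.** If a marker shifts responders up and non-responders down by 0.4 SD in both arms, the SD of the four group means is 0.4, so f = 0.4 and the separation is 0.8 SD. The best possible single-marker rule then has accuracy Phi(0.4) = 65.5%. That ceiling applies before the marker has to be found among other inputs.

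**3. Number of inputs (assumption: 50).** The article does not fix this. Counting one number per listed item gives 15 scales (section 2.4), 6 cognitive measures (2.5), 5 EEG families (2.6) and 13 blood markers (2.7): 15 + 6 + 5 + 13 = 39. Without the blood markers, which section 2.9 does not name as model inputs, it is 26. Both are low, because an EEG family yields several values: connectivity among four regions in two bands is 6 pairs × 2 = 12. If 0.001 is a Bonferroni correction of 0.05, it implies 0.05/0.001 = 50 comparisons.

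**4. Simulated power of the described type of test.** Setup: 1:1 arms, 50% response, independent standard normal inputs, 5-fold shuffled cross-validation, AUC as the statistic. Two learners were used: a random forest (100 trees, treatment as an input) and a ridge logistic model with treatment interactions. The permutation null was approximated by 600 datasets without signal (300 for the several-marker cases). Critical values were the 95th percentile for 0.05 and mean + 3.09 SD for 0.001. There were 200 replicates per one-marker case and 100 per several-marker case. Every informative marker has f = 0.4.

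One informative marker among 50 inputs:

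| Pattern | Learner | N = 144: 0.05 / 0.001 | N = 200: 0.05 / 0.001 |
|---|---|---|---|
| Same direction in both arms | forest | 51% / 8% | 73% / 24% |
| Same direction in both arms | ridge | 32% / 2% | 58% / 10% |
| One arm only | forest | 22% / 3% | 27% / 3% |
| One arm only | ridge | 32% / 5% | 48% / 7% |
| Opposite directions | forest | 6% / 0% | 5% / 0% |
| Opposite directions | ridge | 36% / 3% | 61% / 11% |

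A separate ridge check gave 32-34% (N = 144) and 51-52% (N = 200) at 0.05.

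Several informative markers among 50 inputs, N = 144:

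| Markers | Pattern | forest: 0.05 / 0.001 | ridge: 0.05 / 0.001 |
|---|---|---|---|
| 3 | same direction | 99% / 79% | 92% / 57% |
| 3 | opposite | 6% / 0% | 93% / 44% |
| 5 | same direction | 100% / 99% | 100% / 95% |
| 5 | opposite | 7% / 0% | 100% / 94% |

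With the informative marker as the only input, N = 144 and alpha 0.05, the logistic model has 96-100% and the forest 56-71%.

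Monte Carlo error is at most sqrt(0.5 × 0.5/200) = 3.5 points for one marker and 5 points for several.

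**The case against.** - **A condensed article cannot show that the ANOVA is never run.** This stands. Sections 2.1 and 2.6 make identifying biomarkers an aim, and a per-marker comparison at a corrected alpha would suit it. The full protocol or analysis plan may contain one. The supportable statement is that the article describes none.
- **Much lower power is not a general fact.** This also stands. A reader might infer from the one-marker table that the permutation test always falls far short of 80%, or that the study is underpowered. The documents do not support that. Section 2.9 speaks of predictors in the plural and fixes neither the number of informative markers nor the number of inputs. With three or more markers, most cases at 0.05 exceed 80%.
- **A different alpha cannot be claimed.** Correct: no alpha is printed for the permutation test. The test might also be applied to individual features, since the sentence refers to results in general. Even then it would not be the four-group F test that was sized.
- **The simulation is not the planned procedure.** It uses no nested tuning, neural network or support vector classifier, and the 5% figure comes from one learner under one pattern. The figures are therefore scenarios, not estimates of the trial's power.
- **The tool is not judged by this test alone.** Section 2.1 plans a pilot validation in 20 further patients. That limits the harm, but it does not make the 80% apply to the model.
- **Metric, alpha and input count are usually left to the analysis plan.** True, and their absence is not the complaint. The complaint is that a printed power figure stands beside a test to which it does not belong.

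**Conclusion.** Wrong as written. The arithmetic behind n = 144 is right, but its 80% power belongs to a single-predictor, four-group ANOVA that the article does not describe. It is not the power of the permutation test that the article does describe.

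The size of the gap is conditional. For one f = 0.4 marker among about 50 inputs, acting in both arms and tested at 0.05, power is roughly 30-50% at N = 144 and 50-70% at N = 200. For a marker acting in opposite directions, the pattern most relevant to choosing between treatments, a pooled random forest has about 5%, and it stayed at 7% or below with up to five such markers. A ridge model with interactions does much better, and with several markers either learner can exceed 80% for a same-direction pattern.

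These figures assume independent inputs, no site effects, and complete inputs for all N patients. The last is favourable at N = 200, because section 2.2 describes the 100 retrospective records as clinical data.

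**What to change.** In section 2.9, state that n = 144 and 80% power refer to a single-marker four-group comparison and are not the power of the SelecTool permutation test. Then add one of the following:

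- a simulated power for the test that will be run, stating its cross-validation metric, its alpha, the number of inputs and the n left after losses, for one and for several informative markers, both prognostic and treatment-specific; or
- the expected precision of the cross-validated performance at the available n.

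If a per-marker four-group comparison is planned elsewhere, name it so that the 80% has its own test.

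The cost is a wording change and a short simulation. Enrolment need not change. The downside is a stated power that may be less favourable or depend on the scenario.
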